## Abstract

**Background:**

Despite decades of effort to reduce racial cancer disparities, Black people continue to die at higher rates from cancer than any other U.S. racial group. Because prevention is a key to the cost-effective and long-term control of cancer, the potential for cancer genetic counseling to play a central role in reducing racial cancer disparities is high. However, the benefits of genetic counseling are not equitable across race. Only 2% of genetic counselors self-identify as Black/African American, so most genetic counseling encounters with Black patients are racially discordant. Patients in racially discordant medical interactions tend to have poorer quality patient-provider communication and receive suboptimal clinical recommendations. One major factor that contributes to these healthcare disparities is racial bias. Drawing on findings from prior research, we hypothesize that genetic counselor providers’ implicit racial prejudice will be associated negatively with the quality of patient-provider communication, while providers’ explicit negative racial stereotypes will be associated negatively with the comprehensiveness of clinical discussions of cancer risk and genetic testing for Black (vs. White) patients.

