**Methods:**

Using a convergent mixed methods research design, we will collect data from at least 15 genetic counseling providers, from two different institutions, and their 220 patients (approximately equal number of Black and White patients per provider) whose appointments are for a hereditary cancer condition. The data sources will include two provider surveys, two patient surveys, video- and/or audio-recordings of genetic counseling encounters, and medical chart reviews. The recorded cancer genetic counseling in-person and telehealth encounters will be analyzed both qualitatively and quantitatively to assess the quality of patient-provider communication and the comprehensiveness of clinical discussion. Those data will be linked to pre- and post-encounter survey data and data from medical chart reviews to test our hypotheses.

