Distinguishing these forms of racial bias is important because they are associated with different aspects of healthcare. A recent review [23] provides evidence that providers’ greater implicit prejudice is associated with poorer quality patient-provider communication during racially discordant interactions, [24–28] which can further result in less patient satisfaction and trust in providers (Fig. 1) [29–31]. There is strong evidence that providers’ greater explicit negative stereotyping of Black patients is associated with suboptimal clinical recommendations for Black patients [21, 32, 33]. Drawing on findings from prior research, we developed a conceptual model highlighting genetic counselor bias, particularly implicit prejudice and explicit stereotyping, as major factors contributing to racial disparities in the genetic counseling process. We propose that patient-provider communication will be poorer for Black patients than for White patients (Path A) and that genetic counselors’ implicit prejudice toward Black people is negatively associated with the quality of patient-provider communication for Black patients, but not for White patients (Path C). We also propose that the content of clinical discussions will be lower in quality for Black patients than for White patients (Path B), and genetic counselors’ explicit negative stereotypes about Black people are negatively associated with the quality of clinical discussions for Black patients, but not for White patients (Path D). Finally, lower quality patient-provider communication and clinical discussions, in turn, will lead to Black patients’ negative perception of counselors and genetic counseling encounters (Paths E & F), ultimately contributing to racial disparities in patient-centered outcomes (Path G).

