## Methods

The overarching goal of this research is to compare and contrast the nature of cancer genetic counseling encounters and patient-centered outcomes between Black and White patients in the naturalistic clinical setting. We will test our hypotheses by addressing four specific aims: **Aim 1**) To compare/contrast the nature of patient-provider communication by patient race (Black vs. White); **Aim 2**) To compare/contrast the clinical discussion content by patient race; **Aim 3**) To quantify the role of each type of counselor bias in patient-provider communication (Aim 1) and clinical discussion content (Aim 2); and **Aim 4)** To quantify the role of patient-provider communication and clinical discussion content with patient-centered outcomes (trust, satisfaction, therapeutic alliance, empowerment, genetic testing completion). These aims will be achieved through an observational study with a convergent mixed methods research design. Table 1 provides an overview of the study design.

**Table 1 Tab1:** An overview of the study designs

Aims	Data sources	Analyses	Goals
1	• Recorded encounters	Quantitative analyses of provider communication style and the overall quality of patient-provider communication Qualitative analyses of transcribed encounters for the four basic interaction structures	Identify specific aspects of patient-provider communication during cancer genetic counseling encounters that are different between Black and White patients
2	• Recorded encounters	Qualitative analyses of transcribed encounters for (1) the presence/absence of the key topics for risk communication and genetic test consent during cancer genetic counseling encounters that were identified by NCI; and (2) additional topics discussed during cancer genetic counseling encounters	Identify specific clinical discussion topics during cancer genetic counseling encounters that are different between Black and White patients
3	• Provider baseline survey • Patient baseline survey • Coded encounters	Quantitative analyses of associations between the four forms of provider bias and (1) patient-provider communication as well as (2) clinical discussion content that were identified in Aims 1 & 2	Identify specific aspects of patient-provider communication/clinical discussion topics that contribute to racial disparities in the cancer genetic counseling process and reflect provider bias

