#### Topic comprehensiveness of clinical discussion

Next, we will assess the extent to which topics discussed during clinical encounters are consistent with key topics included in the National Cancer Institute’s (NCI) Cancer Genetics Risk Assessment and Counseling (PDQ®)-Health Professional Version [70]. To do this, two genetic counselors on our team will create a topic codebook based on the PDQ®-Health Professional Version. The codebook will provide coding procedures and rules as well as descriptions and examples of each topic. While the codebook is being developed, two coders will unitize the verbatim transcripts into discrete topics or focal ideas/themes. The coders will be first trained on the unitization with a few transcripts before they start unitizing all transcripts. They will meet every 5 transcripts to discuss and solve discrepancies in the identified thought units. After all the verbatim transcripts are unitized into discrete topics, two coders will be trained on the codebook until they achieve consensus and then code all transcripts independently, while meeting every 10 transcripts to discuss discrepancies and reach consensus. We will use consensus estimates for two reasons. Methodologically, discussion topics are discrete categories [71]. Clinically, providers are expected to discuss with patients each topic clearly and with no ambiguity. Finally, for each encounter, we will create dichotomous (a given topic discussed/not discussed) and continuous (the total amount of time spent on discussing a given topic in seconds) outcomes.

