Aim 2 (to compare/contrast the clinical discussion content by patient race) examines Path B in our conceptual model. We will examine which topics significantly differ between Black and White patients. First, we will identify covariates that may impact clinical discussion content by computing bivariate correlations among all topics and factors assessed in the baseline surveys. All significant factors will be included in the main analyses as covariates. In the main analyses, we will conduct a logistic regression (the dichotomous outcome) and a linear regression (the continuous outcome) for each topic with the main effect of patient race, the main effect of care modality, a two-way interaction between the two and covariates using GEE and the Bonferroni correction.

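### Paths B and D concern comprehensiveness of the clinical discussion, but only single-topic outcomes are analysed; add an encounter-level comprehensiveness score beside them

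*Protocol article*

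**What the plan says.** The Abstract predicts that providers' "explicit negative racial stereotypes will be associated negatively with the comprehensiveness of clinical discussions of cancer risk and genetic testing", for Black compared with White patients. Its Methods paragraph says the recordings will be used to "assess the quality of patient-provider communication and the comprehensiveness of clinical discussion". The Background states Path B as lower-quality discussion for Black patients, and Path D as stereotypes being "negatively associated with the quality of clinical discussions for Black patients, but not for White patients".

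The section on topic comprehensiveness compares each encounter with the NCI key topics. The coding then yields, for each topic, "dichotomous (a given topic discussed/not discussed) and continuous (the total amount of time spent on discussing a given topic in seconds) outcomes". The open-ended list of additional topics is coded in the same way.

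In the Statistical analysis section, Aim 2 reads "we will conduct a logistic regression (the dichotomous outcome) and a linear regression (the continuous outcome) for each topic", each model having race, care modality, "a two-way interaction between the two and covariates using GEE and the Bonferroni correction". For clinical discussion, Table 4 lists only presence and time of a given topic. Aims 3 and 4 work with the topics identified in Aim 2, and their Step 3 models take only those that also pass a partial-correlation step.

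Table 1 gives Aim 2 a topic-level goal: "Identify specific clinical discussion topics during cancer genetic counseling encounters that are different between Black and White patients".

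**The concern.** Comprehensiveness is a property of the whole encounter: how much of what should be covered was covered. None of the listed outcomes measures it. Aim 1 is built differently. Beside its 14 affect categories it has a rating of overall communication quality, so that side of the model has a summary outcome. Clinical discussion has none. This is not a detail left to another document, because the article names the Aim 2 outcomes, models and correction and tabulates the outcome types.

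Two things are at stake. First, if Black patients receive slightly less on most topics, each single difference is small and is judged against a strict threshold. The study may then flag nothing, or flag one or two topics and present a general shortfall as specific to them. Second, the loss carries forward. Table 1 describes Aim 2 as finding topics that differ by race, so a topic not flagged there is not examined for provider stereotyping (Path D) or for patient-centred outcomes (Aim 4).

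**Working it through.** **The plan's own power figure.** The article gives 0.80 power for Cohen's d = 0.2, but for implicit prejudice on communication style. It gives none for Path B or Path D, so there is no figure to reproduce on this point. For scale only, a two-group race contrast of d = 0.2 with 110 per group has noncentrality 0.2 × √(110/2) = 1.48. Its power at two-sided 0.05 is Φ(1.48 − 1.96) = 0.32 before any correction. At 0.05/(2K) it falls to 0.05 for K = 15 and 0.03 for K = 30.

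**Inputs**
- From the article: 220 patients, about equal by race, so 110 versus 110; two outcomes per topic; Bonferroni.
- Assumed: K = 15, 20 or 30 topics; one family of 2K tests; two-sided 0.05; White patients receive each topic with probability 0.85; topics within an encounter share a latent (probit) correlation of 0.15 or 0.5; no provider clustering, covariates or race-by-modality term.

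**Per-topic power (presence outcome).** Power ≈ Φ{[Δ − z·√(2p̄(1−p̄)/n)] / √[(p₁(1−p₁)+p₂(1−p₂))/n]}, where z is the critical value at α = 0.05/(2K).

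For K = 20, α = 0.05/40 = 0.00125 and z = 3.227.
- 0.85 v 0.80: (0.05 − 3.227 × 0.0512)/0.0511 = −2.26, so power is about 1.2%.
- 0.85 v 0.75: (0.10 − 3.227 × 0.0539)/0.0535 = −1.38, so power is about 8.3%.

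**Any-topic and score power, by simulation.** Any-topic power is the chance that at least one presence test passes 0.05/(2K). The score is the share of topics covered per encounter, compared by one t-test at 0.05. Ranges are over K = 15 to 30.

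| Scenario | One given topic | Any topic flagged | Share score |
|---|---|---|---|
| All topics 0.85 v 0.80, correlation 0.15 | about 1% | 18–22% | 77–85% |
| All topics 0.85 v 0.75, correlation 0.15 | 6–10% | 73–79% | over 99% |
| Two topics 0.85 v 0.60, rest equal, correlation 0.15 | 80–86% | 96–98% | 19–44% |

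At correlation 0.5 the score's power is 38–43% for 0.85 v 0.80 and 89–90% for 0.85 v 0.75. Power for one given topic does not depend on the correlation.

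**What is carried forward.** In the uniform 0.85 v 0.75 case, the expected number of topics flagged on presence is K × per-topic power: 15 × 0.094 = 1.4 and 30 × 0.064 = 1.9. All K topics truly differ, but about one or two would usually reach Aims 3 and 4.

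**Path D.** A separate simulation used a continuous topic outcome, 15 providers, no within-provider correlation and K = 10. A topic had to pass the Aim 2 race test and then show a race-by-stereotyping interaction at 0.05. The partial-correlation step was left out.
- Race effect and interaction both 0.2 SD: 2% of runs succeed.
- Race effect 0.5 SD and interaction 0.3 SD: 45% succeed.

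**The case against.** The strongest reply is that topic-level analysis is deliberate. Table 1 and Aim 2 ask which topics differ, and the Discussion wants lists of topics to cover and topics that may be left out. A total score cannot supply those. The Background also words Paths B and D as quality, not as a count, so the share of key topics is one way to define the construct and not the article's own. This stands, and it is why the topic models should stay and not be demoted.

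A reader might infer that the hypothesis is never tested. That goes too far: it is tested topic by topic, though not in aggregate. A reader might also infer that the plan has almost no power for Paths B and D. The document does not support that either, because it gives no number of topics, no family and no expected topic rates. In the uniform 0.85 v 0.75 case at least one topic is flagged in 73–79% of studies. For a continuous topic outcome with d = 0.5, per-topic power is 0.82 with 5 topics and 0.64 with 30. Nor is the correction the only cause, since an uncorrected d = 0.2 contrast has only 0.32.

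Finally, the score gains only when differences run the same way across topics, and gains most when topics are weakly correlated. With the difference in two topics the ranking reverses.

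**Conclusion.** The gap between construct and outcome is in the text and does not depend on any power figure: comprehensiveness is hypothesised, and no encounter-level measure of it is analysed. The consequence is conditional. The clearest loss is for small differences spread over many topics, where a score has roughly four times the any-topic power at correlation 0.15 (77–85% against 18–22%). For larger uniform differences the main harm is misreading: a general shortfall appears as one or two topics, and the rest drop out of Aims 3 and 4. For concentrated differences the existing tests are the better tool.

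The figures rest on the assumed number of topics, the assumed family of 2K tests, the assumed topic rates and the absence of clustering and covariates. The any-topic figures count presence tests only, so adding the time outcomes could raise them. The two analyses answer different questions, and the plan needs both.

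**What to change.** Prespecify one comprehensiveness outcome: the share of NCI key topics discussed in each encounter, computed from the presence codes and leaving out the later additional topics.

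- **Path B:** test its race effect once in Aim 2.
- **Path D:** test its race-by-explicit-stereotyping interaction once in Aim 3. The article computes a general and a medicine-specific stereotype composite, so name the one used for this test.
- **Carry-forward:** take the score into Aims 3 and 4 whatever the per-topic results.
- **Topic models:** keep them for the stated goal of identifying specific topics, and state the family. Bonferroni is valid there. Holm may replace it, since it keeps the same family-wise control and never has less power.
- **Error control:** say whether the score test has its own 0.05, as assumed in the figures above, or shares the topic family.

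The cost is one variable derived from data already coded and one more prespecified test for each path. No new data are needed.

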On the day of the appointment, the patient-genetic counseling provider clinical encounter will be video- and audio-recorded. *For patients who have appointments in-person*, we will use two GoPro10 cameras (one focusing on the patient, another focusing on the provider) mounted on the wall with Velcro. These portable devices are designed to minimize intrusiveness while capturing patient-provider communication. We will attach the two cameras to the walls of the consultation room prior to the patient entering. The genetic counseling provider and patient will meet as scheduled while we control the recording from outside of the room using a GoPro device called The Remote [45]. Additionally, a digital voice recorder will capture audio of the interaction to be used in the unlikely event that the video fails. After each encounter, the genetic counseling provider will complete a 1-minute post-encounter survey, and the patient will be escorted to another room to complete a 5-minute post-encounter survey. Both the provider and the patient will be given three options to complete the survey: [1] paper and pencil, [2] a tablet with optional stylus, and [3] a QR code to scan and complete the survey on a personal device.

*For patients who have appointments via telehealth*, we will record the encounters locally on a laptop using Camtasia® screen capture software [46]. We will join the virtual appointment with both camera and microphone turned off. The patient and provider will meet as they typically would, and we will capture a screen recording of the appointment using Camtasia. Immediately after the telehealth encounter, the provider will receive a link to the provider post-encounter survey, and the patient will receive a phone call to complete the patient post-encounter survey over the phone. Providers will receive $30 after completing the provider baseline survey, and patients will receive $30 after completing the post-encounter survey.

Finally, we will review electronic medical records to assess whether patients agreed to take a genetic test after the recorded pre-test genetic counseling session. We will also assess genetic testing completion up to 6 months after the recorded genetic counseling session by reviewing patient electronic medical records (0 = test not completed, 1 = test completed).

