#### Patient-provider communication quality

The quality of patient-provider communication will be analyzed in two ways: global affect and linguistic patterns. To assess global affect, we will observe recordings and rate genetic counseling providers’ communication style by using the Global Affect Ratings from the Rotor Interaction Analysis System (RIAS) [47]. RIAS is the most commonly used method for coding genetic counseling encounters, [35, 36, 48] so use of RIAS enables us to directly compare our findings to those from prior research. We will use the Global Affect Ratings because the ratings reflect not only verbal behaviors (i.e., the context of speech) but also nonverbal (e.g., eye gaze, body posture, hand gestures) and paraverbal (e.g., tone, pitch, speed) behaviors, which tend to reflect an individual’s implicit prejudice [18–20]. The Global Affect Ratings consists of 14 categories: responsiveness/engagement; dominance/assertiveness; anger/irritability; anxiety/nervousness; hurried/rushed; friendliness/warmth; interest/attentiveness; depression/sadness; sympathy/empathy; emotional distress/upset; respectfulness; interactivity; scriptedness; and spontaneity. We will add a rating to assess the overall quality of patient-provider communication (e.g., smooth, awkward, good quality).

Each encounter will be rated by 15 racially diverse female coders. Coders will be all female because prior research has shown that women are more likely than men to make more accurate judgments of others’ characteristics [49]. Research has shown that over-thinking and over-reasoning can often disrupt the accuracy of global judgements and that people usually make better judgments when they do not try to explain their judgments [49–51]. Thus, we will not train coders to identify specific behaviors that might play role in making global judgments (e.g., smiling, frowning, eye contact). We will simply instruct them to report their impressions by using the full scale [24]. Coders will view encounters one by one and provide their ratings first for the 14 categories and then the additional items to assess overall patient-provider communication. The presentation order of the encounters will be randomized across coders. We will compute a composite score for each affective category and the overall patient-provider communication by averaging the ratings across coders. This composite score will be used in the statistical analysis.

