Aim 1 (to compare/contrast the nature of patient-provider communication by patient race) examines Path A in our conceptual model. To test Path A, first, we will examine a numerical and graphical summary of descriptive statistics that will inform the distribution of the 15 outcomes (14 categorical variables and the overall patient-provider communication) and that may require data transformation. Then, we will conduct two separate analyses for communication and linguistic patterns. To examine how genetic counseling providers’ communication style differs by patient race, we will identify covariates by conducting bivariate correlations among all 15 outcomes and factors that were assessed in the baseline surveys (e.g., provider/patient demographics including sex, provider professional characteristics, patient perceived discrimination). Next, we will estimate a linear regression model for each outcome with the main effect of patient race, the main effect of care modality, a two-way interaction between patient race and care modality, and covariates identified as highly correlated with the outcomes. We will use GEE (which controls for the dependence in outcomes due to patients nested within providers) in these regressions, instead of multilevel modeling (which models the nonindependence in data), because there will not be enough upper-level units (i.e., counselors) to model random effects in our data. We will use the Bonferroni correction [93, 94] to address family-wise errors due to multiple comparisons. To examine which specific linguistic patterns differ by patient, we will conduct analyses in similar steps described above. First, we will identify highly correlated covariates by computing bivariate correlations among all quantified linguistic patterns and factors assessed in the baseline surveys. Next, we will conduct a regression for each quantified linguistic pattern with the main effect of patient race, the main effect of care modality, a two-way interaction between the two, and covariates using GEE and the Bonferroni correction. Type of regressions will depend on the measurement units.

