Aim 3 (to quantify the role of each type of counselor bias in patient-provider communication and clinical discussion content) examines Paths C and D in our conceptual model. Analyses will be carried out in three steps. In Step 1, we identify covariates associated with patient-provider communication or clinical discussion content. We will compute correlations among all facets of patient-provider communication/clinical discussion topics identified in Aims 1 & 2 and factors assessed in the baseline surveys (e.g., provider/patient demographics, provider professional characteristics, patient perceived discrimination). In Step 2, we compute partial correlations between all forms of provider bias and aspects of patient-provider communication/clinical discussion topics identified in Aims 1 & 2, controlling for covariates that were significantly associated with any of the provider behaviors. In Step 3, we conduct two regressions for each of the specific aspects of patient-provider communication and clinical discussion topics that remain statistically significant in Step 2. One regression will focus on the role of provider prejudice and will consist of four main effects (patient race, provider implicit prejudice, provider explicit prejudice, care modality), all six combinations of two-way interactions, all four combinations of three-way interactions, and one four-way interaction among all predictors. The second regression model will focus on the role of provider stereotyping and will consist of four main effects (patient race, provider implicit stereotyping, provider explicit stereotyping, care modality), all six combinations of two-way interactions, four combinations of three-way interactions, and one four-way interaction among all predictors. The type of each outcome, summarized in Table 4, will determine the regression model to analyze. The regressions will also include the same set of covariates as in Step 2. All four types of provider bias will be grand-mean-centered. We will use GEE and the Bonferroni corrections in analyses. The provider communication styles that remain statistically significant in Step 3 are considered as key communication styles that contribute to racial disparities in the cancer genetic counseling process and reflect provider bias.

**Table 4 Tab4:** An overview of the outcomes and analyses for each aspect of patient-provider communication and clinical discussion content

Outcome types	Variables	Analytical approaches

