Continuous: Likert scale	*Patient-provider communication* (Provider communication style; The overall quality of patient-provider communication)	Linear regression with GEE
Continuous: Frequency	*Patient-provider communication* (Each type of silence; Each type of adjacency pairs; Each type of problems)	Poisson regression with GEE
Continuous: Proportion	*Patient-provider communication* (Topics initiated by providers; Primary units allocated to providers; Silence followed by provider talks; Repairs initiated by providers; Problems repaired by providers)	Linear regression with GEE
Continuous: Duration	*Patient-provider commu*nication (Each type of silence) *Clinical discussion con*tent (The amount of time spent on discussing a given topic)	Linear regression with GEE
Dichotomy	*Clinical discussion content* (The presence/absence of a given discussion topic)	Logistic regression with GEE
Multiple categories	*Patient-provider communication* (The primary units of turns)	Multinomial logistic regression with GEE

Finally, Aim 4 (to quantify the impact of patient-provider communication/clinical discussion content with patient-centered outcomes) examines Paths E and F in our conceptual model. The analyses will be carried out in steps similar to those in Aim 3. In Step 1, we will identify covariates associated with patient-centered outcomes by computing correlations among all aspects of patient-provider communication/clinical discussion topics and factors assessed in the patient baseline survey, the provider baseline survey, and the provider post-encounter survey. In Step 2, we will compute partial correlations between all aspects of patient-provider communication/clinical discussion topics identified in Aims 1 and 2 and patient-centered outcomes while controlling for covariates identified in Step 1. In Step 3, we will conduct a linear regression with GEE and Bonferroni correction for each self-reported outcome (e.g., trust, satisfaction, therapeutic alliance) and a logistic regression with GEE for behavioral outcome (genetic testing completion). All regressions will include the same set of predictors (aspects of patient-provider communication/clinical discussion topics that remain significant in Step 2, and care modality) and covariates. Aspects of patient-provider communication/clinical discussion topics that remain significant in Step 3 are considered as potentially important intervention points for reducing racial disparities in patient-centered outcomes.

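### Care modality is missing from the Step 2 partial correlations that decide which items Aims 3 and 4 go on to test, although every other model in the plan includes it; the risk is greatest in Aim 4.

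*Protocol article*

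**What the plan says.** All references are to the protocol article.

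- **Aims 1 and 2 (Statistical analysis).** Each Aim 1 regression contains "the main effect of patient race, the main effect of care modality, a two-way interaction between patient race and care modality". The Aim 2 models contain the same terms.
- **Aim 3.** Step 1 looks for covariates among factors measured in the baseline surveys. Step 2 computes partial correlations between provider bias and the communication aspects or topics, "controlling for covariates that were significantly associated with any of the provider behaviors". Only items still significant in Step 2 go to the Step 3 regressions, where modality enters as a main effect and in the interactions.
- **Aim 4.** Step 1 searches the patient baseline, provider baseline and provider post-encounter surveys. Step 2 correlates communication aspects and topics with "patient-centered outcomes while controlling for covariates identified in Step 1". Step 3 contains the items that survive Step 2, plus care modality.
- **Recording (Data collection).** For in-person visits, "we will use two GoPro10 cameras (one focusing on the patient, another focusing on the provider) mounted on the wall with Velcro". For telehealth visits, "we will capture a screen recording of the appointment using Camtasia".
- **Post-encounter survey (Data collection).** In-person patients complete it themselves on paper, a tablet or a personal device. After a telehealth visit, "the patient will receive a phone call to complete the patient post-encounter survey over the phone".
- **Affect ratings (Patient-provider communication quality).** They were chosen because "the ratings reflect not only verbal behaviors (i.e., the context of speech) but also nonverbal (e.g., eye gaze, body posture, hand gestures" and similar cues, and also tone, pitch and speed.

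Care modality is a feature of the encounter. It is not among the survey variables in Table 2 or in the Measures section.

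**The concern.** The plan treats modality as a necessary control everywhere except in the one step that discards items. As written, Step 1 cannot select it, because it searches only survey factors, so Step 2 correlates measures pooled over two visit types without adjustment.

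If modality shifts both variables in a correlation, the pooled correlation mixes the within-modality association with the difference between modalities. A null association can then pass, or a true one can fail. The two errors have different consequences. A false pass meets modality again in Step 3 and can be removed there. A false exclusion is final, because the item never reaches a model that holds modality. Step 3 survivors become the key communication styles (Aim 3) and the possible intervention points (Aim 4), so a lost item is lost to the study's conclusions.

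**Working it through.** **1. Where modality is controlled.**

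| Analysis | Source of covariates | Modality included? |
|---|---|---|
| Aim 1 and Aim 2 models | baseline surveys | yes, with race interaction |
| Aim 3 Step 2 | Step 1, baseline surveys | no |
| Aim 3 Step 3 | as Step 2 | yes, with interactions |
| Aim 4 Step 2 | Step 1, three surveys | no |
| Aim 4 Step 3 | Step 1, plus Step 2 survivors | yes |

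**2. Can modality move both variables?**

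- *Aim 4: plausibly yes.* The communication measure comes from wall cameras or from a screen recording. The patient-reported outcome comes from a self-completed form or a phone call. The survey-mode route does not apply to genetic testing completion, which is read from the medical record.
- *Aim 3: only indirectly.* Bias is a provider score taken at baseline, before the first recorded visit, so the modality of an encounter cannot change it. Confounding requires providers with higher bias to have a different telehealth share. Otherwise modality only adds variance to the communication measure.

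**3. Size, for Aim 4.** The article gives no figure to reproduce here. From the document: n = 220. Assumed: independent patients, two-sided 0.05 at Step 2, within-modality correlation r = 0.20 (or 0), telehealth share p, and modality shifts of dx and dy within-modality SDs. With c = p(1 − p):

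pooled r = (r + c·dx·dy) / √[(1 + c·dx²)(1 + c·dy²)]

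pass probability = Φ(z − 1.96) + Φ(−z − 1.96), where z = √(n − 3)·atanh(pooled r)

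With modality adjusted, one more degree of freedom is used: z = √216 × atanh(0.20) = 14.70 × 0.2027 = 2.98, giving 0.85.

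Unadjusted example, p = 0.5, shifts 0.5 and −0.5 SD: pooled r = (0.20 − 0.0625)/1.0625 = 0.129; z = √217 × 0.1301 = 1.92; pass probability 0.48.

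| Shifts (SD), telehealth share | r = 0.20, opposite: pooled r | r = 0.20, opposite: pass | r = 0.20, same direction: pass | r = 0, same direction: false pass |
|---|---|---|---|---|
| Modality adjusted | 0.200 | 0.85 | 0.85 | 0.05 |
| 0.2 / 0.2, 50% | 0.188 | 0.80 | 0.87 | 0.052 |
| 0.5 / 0.5, 20% | 0.154 | 0.63 | 0.93 | 0.09 |
| 0.5 / 0.5, 50% | 0.129 | 0.48 | 0.96 | 0.14 |
| 0.8 / 0.5, 50% | 0.090 | 0.265 | 0.98 | 0.265 |

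**4. Noise only, as in Aim 3 with an even modality mix.** Put dx = 0, dy = 0.5, p = 0.5: pooled r = 0.20/√1.0625 = 0.194 and the pass probability is 0.83, against 0.85. The loss is small. Treating patients as independent is least realistic here, because bias takes only as many values as there are providers (at least 15).

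**The case against.** The strongest reply is that the final inference is already adjusted. Items enter Step 2 from Aim 1 and 2 models that contain modality, and Step 3 contains it again. This holds for the final estimates and for false passes. It does not answer false exclusion: the Aim 1 and 2 models test race differences and leave the Step 2 correlations unadjusted.

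Several further points stand and limit the concern:

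- Losing a true positive association requires modality to move the two variables in opposite directions. The article gives no reason to expect that. Same-direction shifts make a true association more likely to pass.
- The shift sizes and telehealth shares are assumptions. Half telehealth maximises p(1 − p), so it is the worst share. With small shifts, 0.85 falls only to 0.80.
- Patients are nested within providers, so the figures illustrate direction and order of size. They are not the study's operating characteristics.

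A reader might infer three stronger things that the article does not support. First, that telehealth recordings hide behavior that the cameras capture: the article does not describe the telehealth picture. The inference is reasonable for gaze, posture and gesture, but weak for tone and for the transcript and topic measures. A modality difference may also be a real difference in the encounter. Second, that Aim 3 is as exposed as Aim 4: it is not, because encounter modality cannot shift a baseline bias score. Third, that audio-only encounters must leave the affect analyses. The abstract does allow "video- and/or audio-recordings of genetic counseling encounters", but for in-person visits audio is a backup for a video failure that the article calls unlikely. That is a separate matter, and nothing here requires the exclusion.

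The reply that an article condenses the full plan also has limited force. The article states the adjustment set for each step, and the Step 2 set does not match the others.

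**Conclusion.** The inconsistency is real. Step 2 of Aims 3 and 4 decides which items are tested, it omits a control that all the other models carry, and Step 1 as described cannot supply it. The main consequence is that an item can be dropped without ever being examined in a modality-adjusted model.

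The weight falls on Aim 4, for the patient-reported outcomes. There the effect ranges from minor to serious, depending on modality shifts that the article does not give and that would have to run in opposite directions to hide a positive association. In Aim 3 confounding is conditional on how modality is distributed across providers; failing that, the cost is a little precision. The Step 3 estimates themselves are not left unadjusted. This is worth correcting because the correction is simple, not because harm has been shown.

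**What to change.** State that care modality is a fixed control in every Step 2 partial correlation of Aims 3 and 4, whatever Step 1 selects, to match Step 3. Modality is already recorded for every encounter, since the Aim 1 and 2 models need it. The cost is one degree of freedom per correlation. No data collection changes, and no encounters need to be excluded.
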